### Outcome measures and data collection

Follow-up data collection is by postal questionnaire. The outcome measures are detailed in Table 2. The primary outcome is return to normal function after the whiplash injury, measured using the Neck Disability Index (NDI). The NDI is a self-completed questionnaire that has been used successfully in a postal format in trials of neck treatments[10,17]. It assesses pain-related activity restrictions in 10 areas including personal care, lifting, sleeping, driving, concentration, reading and work. The SF-12 and EQ-5D are included to assess generic health-related quality of life, and to enable a single utility score for economic evaluation to be derived from the EQ-5D. Participants also rate whether they have improved, remained the same, or worsened, and their satisfaction with treatment. Resource use is assessed by a short questionnaire which asks about additional NHS or private hospital treatment for the whiplash injury, any GP consultations, manipulation, massage or other treatment. Participants are asked to distinguish between prescription and out-of-pocket expenses.

Participants are asked at 12 month follow-up whether they have pursued and settled a compensation claim related to their whiplash injury. It is not asked at 4 or 8 month follow-up to avoid stimulation of claims among the trial population.

A research assistant who has not been involved in the recruitment or randomisation processes is responsible for mailing follow up questionnaires, and for entering responses onto the study database. Blinding of the study team will be maintained until final analysis of the data has been completed.

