### Statistical analysis

The analysis will be by intention to treat. All patients will be analysed in the groups to which they were randomised, regardless of the treatment that they actually received. The two main comparisons will be Whiplash Book versus usual advice, and physiotherapy package versus reinforcement of ED advice. The comparison of ED advice interventions will use appropriate methods to take account of the cluster randomisation[18]. Estimates of treatment effect with 95% confidence intervals, and the numbers needed to treat, will be reported. Additional exploratory analyses will investigate whether there is an interaction between the ED advice intervention and physiotherapy.

Four pre-specified subgroup analyses will be undertaken:

1. severe physical symptoms at trial entry (WAD Grade III versus WAD Grade I or II)

2. adverse psychological reactions at trial entry (yes/no)

3. pre-existing neck pain versus no pre-existing neck pain

4. compensation; claim being pursued versus not being pursued

Statistical tests of interaction will be used to perform subgroup analyses[19].

Economic analysis will use cost-minimisation, or cost-effectiveness and cost-utility analysis, depending on the clinical results. For cost-utility analysis, the EQ-5D will be used to generate utility scores, which will provide an estimate of the incremental cost of any benefit gained in terms of improved health status. Decision modelling will be used to investigate the costs and benefits of the different patient management routes, and uncertainty will be quantified by multi-way sensitivity analyses[20].

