### Sample size

For the primary outcome of NDI, there is consensus that a minimal clinically importance difference lies in the range of 3–5 percentage points, with a standard deviation of about 8%[8]. We therefore aim to be able to detect a difference between the groups of three percentage points (i.e. 0.375 standard deviations), both for the comparison of the Whiplash Book and usual advice, and for physiotherapy versus reinforcement of advice. For the individually randomised comparison (physiotherapy versus reinforcement of advice), 211 per group will be required, based on 90% power and 1% significance level. Assuming a worst case scenario of 30% loss to follow-up gives a total sample size of 300 per group (600 in total)[21]. The comparison of ED advice interventions is cluster randomised, so larger numbers are needed. Originally it was planned that eight centres would participate, recruiting 4,800 participants. This was revised with the inclusion of four additional centres, which allowed reduction of the overall sample size required to achieve the same power. Assuming an intra-cluster correlation co-efficient of 0.02, and an average of 120 patients per centre gives an inflation factor of 5.94[22], leading to a sample size of 713 in each group. Allowing for 30% loss to follow up, 1020 participants per group will be needed (2040 in total). To allow for a reduction in power caused by unequal sample sizes among clusters, the target sample size has been set to 3000 (an average of 250 per cluster). The assumptions underlying the sample size calculation will be monitored by the DMEC during recruitment and adjustments may be made during the course of the trial.

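### The choice between cost-minimisation and cost-utility analysis should not depend on the clinical results, because the trial is not designed to show equal benefit

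*Protocol article*

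**What the plan says.** The Statistical analysis section of the protocol article states: "Economic analysis will use cost-minimisation, or cost-effectiveness and cost-utility analysis, depending on the clinical results". It does not say which result would lead to cost-minimisation. If cost-utility analysis is done, utilities come from the EQ-5D, which Outcome measures and data collection says is included "to enable a single utility score for economic evaluation to be derived from the EQ-5D". Decision modelling is planned as well, and "uncertainty will be quantified by multi-way sensitivity analyses".

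The Sample size section sets the design for both comparisons: "We therefore aim to be able to detect a difference between the groups of three percentage points (i.e. 0.375 standard deviations"). The reason given is that "a minimal clinically importance difference lies in the range of 3–5 percentage points, with a standard deviation of about 8" per cent. No equivalence or non-inferiority margin, and no equivalence analysis, appears anywhere in the article. Clinical effects are to be reported with 95% confidence intervals.

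**The concern.** Cost-minimisation is valid only where the arms can be taken to have equal health effects. It then sets the health difference to zero and ranks the arms on cost. A trial sized to detect a difference gives no warrant for that step when it fails to find one: a null result leaves a range of effects open, and the best estimate of the difference is seldom exactly zero.

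The primary clinical outcome and the measure of economic benefit also differ. The NDI records neck-related disability, and the EQ-5D supplies the utility. Even a precise NDI result does not limit how far the arms may differ in QALYs.

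The stakes are clearest in Stage 2, where up to six physiotherapy sessions are compared with one 40-minute advice session. On delivery cost alone, a ranking by cost favours advice wherever the EQ-5D estimate falls. The costs and cost-effectiveness of each strategy are a stated aim of the trial (opening of Methods), so the form of this analysis matters, although the primary clinical analysis is not affected.

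**Working it through.** **Inputs (Sample size section).** Target difference 3 points; SD 8; 1% significance level; 90% power; 30% loss. Sidedness is not stated; a two-sided test reproduces the figure, and a one-sided test gives 186.

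**1. The plan's own figure.** The article says "211 per group will be required, based on 90% power and 1% significance level".

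n per group = 2 × (2.576 + 1.282)² / 0.375² = 211.6, which rounds up to 212. This agrees with 211.

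For attrition: "Assuming a worst case scenario of 30% loss to follow-up gives a total sample size of 300 per group (600 in total"). 211 / 0.7 = 301.4, so 302 after rounding up, close to 300. Conversely, 300 × 0.7 = 210 analysed per arm, which is used below.

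**2. Stage 2 precision.** SE = 8 × √(2/210) = 0.781 points. The 95% half-width is 1.96 × 0.781 = 1.53. The significance boundary at 1% is 2.576 × 0.781 = 2.01.

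**3. Chance of a non-significant result when a real effect exists.** P = Φ(c − d/SE) − Φ(−c − d/SE), with c = 1.960 or 2.576 and d the true difference. For d = 1.5, d/SE = 1.921, so P = Φ(0.039) = 52% at the 5% level and Φ(0.655) = 74% at 1%.

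| True NDI difference | 5% level | 1% level |
|---|---|---|
| 1 | 75% | 90% |
| 1.5 | 52% | 74% |
| 2 | 27% | 51% |
| 3 | 3% | 10% |

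**4. What a non-significant Stage 2 result rules out.** If it is non-significant at 5%, the estimate is at most 1.53 and the upper 95% limit at most 1.53 + 1.53 = 3.06. If it is non-significant only at 1%, the estimate can be 2.01 and the limit 2.01 + 1.53 = 3.54. The share of non-significant results whose 95% interval still reaches 3 points is:

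| True NDI difference | 5% level | 1% level |
|---|---|---|
| 0 | 1% | 5% |
| 1.5 | 6% | 35% |
| 2 | 9% | 51% |

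At the 5% level, then, a null Stage 2 result says much about a 3-point NDI effect and little about a 1- to 2-point effect.

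**5. Stage 1.** No single figure can be given, because it depends on choices that the article leaves open. The article says: "Assuming an intra-cluster correlation co-efficient of 0.02, and an average of 120 patients per centre gives an inflation factor of 5.94". Those inputs give 1 + (120 − 1) × 0.02 = 3.38, and it is 3.38 that yields the stated 713 (211 × 3.38 = 713). Assume six Trusts per arm, an intra-cluster correlation of 0.02, m analysed per Trust and an unpaired t test on 10 df. Then SE = 8 × √(2 × (0.02 + 0.98/m)/6). For a true 3 points, P(non-significant) is 5% with m = 175 (250 × 0.7) at the 5% level, 21% with m = 175 at 1%, and 26% with m = 120 at 1%. Trusts were matched in pairs, and a paired analysis would have only 5 df, so even this range is not firm.

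**6. Economic consequence.** The article gives no cost, utility or willingness-to-pay value, so the chance of a wrong economic conclusion cannot be worked out.

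**The case against.** The strongest reply is that the article contains no rule of the form *NDI non-significant, therefore equal*. A reader might infer that the plan treats a null NDI test as proof of equality. The text does not support this: it refers only to the clinical results, which may include the EQ-5D and SF-12, and a fuller plan may define the trigger. This stands, and the trigger described here is an inference. It does not remove the point, because any definition of the trigger would still let results choose the method, and nothing in the article would establish equality.

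Second, the 1% level appears only as a sample-size input, whereas reporting uses 95% intervals. At 5% the probabilities are smaller, and a null Stage 2 result nearly always excludes 3 points, the lower end of the stated range of important differences. This also stands. It limits the concern to smaller NDI effects and to QALYs, which the NDI does not bound.

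Third, a reader might infer that the rule is certain to favour advice, or that the EQ-5D data are thrown away. Neither follows. The section on Other treatments expects effective treatment to reduce additional care, so total costs may not follow session counts. The EQ-5D also remains a quality-of-life outcome, and decision modelling of costs and benefits is planned without condition.

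Finally, resampling methods, acceptability curves and the handling of clustering in the cost model are details that an article commonly leaves to the full plan. They are not raised as faults.

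**Conclusion.** The concern holds in a limited form. What is at fault is a stated rule: the form of the economic analysis follows the clinical results, and one option assumes equal benefit in a trial designed to detect a difference, with no equivalence margin.

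The Stage 2 figures (52% non-significant at a true 1.5 points and 3% at 3 points at the 5% level; 74% and 10% at 1%) rest on SD 8, 210 analysed per arm, a two-sided normal test, and the assumption that lack of significance on the NDI is what would lead to cost-minimisation. They show that a null result is weak evidence against small effects. They do not show that the economic conclusion would be wrong. A reader might go that far, but the documents support only the possibility.

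The change should be made. It bears on a stated aim of the trial and leaves the clinical analysis untouched.

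**What to change.** Delete the conditional choice and the cost-minimisation option from the Statistical analysis section. State instead that incremental cost and incremental EQ-5D QALYs will be estimated jointly, with their uncertainty, for both the ED advice comparison and the physiotherapy comparison, whatever the clinical result. Keep the multi-way sensitivity analyses as a supplement. If the QALY difference proves small, the joint estimate will show that, together with how precisely it is known.

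The cost is a little more analysis. EQ-5D and resource use are already collected, so no new data, participants or follow-up are needed.

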### Sample size

For the primary outcome of NDI, there is consensus that a minimal clinically importance difference lies in the range of 3–5 percentage points, with a standard deviation of about 8%[8]. We therefore aim to be able to detect a difference between the groups of three percentage points (i.e. 0.375 standard deviations), both for the comparison of the Whiplash Book and usual advice, and for physiotherapy versus reinforcement of advice. For the individually randomised comparison (physiotherapy versus reinforcement of advice), 211 per group will be required, based on 90% power and 1% significance level. Assuming a worst case scenario of 30% loss to follow-up gives a total sample size of 300 per group (600 in total)[21]. The comparison of ED advice interventions is cluster randomised, so larger numbers are needed. Originally it was planned that eight centres would participate, recruiting 4,800 participants. This was revised with the inclusion of four additional centres, which allowed reduction of the overall sample size required to achieve the same power. Assuming an intra-cluster correlation co-efficient of 0.02, and an average of 120 patients per centre gives an inflation factor of 5.94[22], leading to a sample size of 713 in each group. Allowing for 30% loss to follow up, 1020 participants per group will be needed (2040 in total). To allow for a reduction in power caused by unequal sample sizes among clusters, the target sample size has been set to 3000 (an average of 250 per cluster). The assumptions underlying the sample size calculation will be monitored by the DMEC during recruitment and adjustments may be made during the course of the trial.

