#### Randomisation

The unit of randomisation is the NHS Trust. Participating Trusts were randomised before the start of recruitment by the project statisticians, to usual advice or the Whiplash Book. Trusts were pair matched on size (number of ED attendances per year), star rating, and ethnic composition of the surrounding area. We randomised by Trust rather than by ED to avoid contamination when staff of one Trust worked in more than one ED. Randomisation used a table of random numbers, starting at a random place to ensure that the allocations were not known before randomisation. The allocation depended on whether the next digit was even or odd. One of each pair was randomised to the Whiplash Book, and the other member was allocated to usual advice.

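### The Stage 1 sample size claims 90% power at the 1% level without allowing for only 12 randomised Trusts; an unmatched analysis has about 79%

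*Protocol article*

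**What the plan says.** The Sample size section sets one target for both main comparisons: to "detect a difference between the groups of three percentage points (i.e. 0.375 standard deviations"), "with a standard deviation of about 8" percentage points. For the individually randomised Stage 2, "211 per group will be required, based on 90% power and 1% significance level".

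For Stage 1 the section begins "Assuming an intra-cluster correlation co-efficient of 0.02", takes an average of 120 patients per centre, and arrives at 713 per group. It then allows for 30% loss to reach 1,020 per group (2,040 in total). It says that four added centres "allowed reduction of the overall sample size required to achieve the same power". The last step is "To allow for a reduction in power caused by unequal sample sizes among clusters, the target sample size has been set to 3000". Spread over 12 Trusts, that comes to 250 each.

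The Methods section lists 12 Trusts. The Stage 1 Randomisation section makes the Trust the unit of randomisation and says that "Trusts were pair matched on size (number of ED attendances per year), star rating, and ethnic composition of the surrounding area", with one of each pair allocated to each arm. The Statistical analysis section says: "The comparison of ED advice interventions will use appropriate methods to take account of the cluster randomisation[18]". It plans 95% confidence intervals.

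**The concern.** A design effect corrects the variance of the treatment comparison for clustering. It does not correct the reference distribution. When 12 units are randomised, the between-Trust error is estimated from very few values: 10 degrees of freedom if the pairs are ignored and 5 if they are kept. At the 1% level this matters a good deal. The two-sided critical value is 2.576 for the normal distribution, 3.17 on 10 degrees of freedom and 4.03 on 5.

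Stage 1 is one of the trial's two main comparisons. If its power at the stated level is overstated, a null result judged at 1% would be given more weight as evidence of no 3-point difference than the design can bear.

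**Working it through.** **Inputs from the protocol.** Difference 3 points, SD 8 (standardised difference 0.375), level 1% (two-sided reproduces the printed figure), power 90%, ICC 0.02, loss 30%, 12 Trusts (6 per arm), target 3,000. Analysed per Trust: 3,000 × 0.7 / 12 = 175. Equal cluster sizes are assumed unless stated.

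**1. Reproducing the plan's figures.**
- Individual n per group: 2 × (2.576 + 1.282)² / 0.375² = 211.6 (printed: 211).
- Design effect at 120 per cluster: 1 + 119 × 0.02 = 3.38.
- 211 × 3.38 = 713 (printed: 713). 713 / 0.7 = 1,019 (printed: 1,020).

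So the Stage 1 number follows from 90% power, the 1% level and a normal critical value. The printed inflation factor of 5.94 does not belong to 120 per cluster or to 713. It is the design effect for 248 per cluster (1 + 247 × 0.02). That is a separate slip and is not used below.

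**2. Power at the full 3,000 target.**
- Design effect: 1 + 174 × 0.02 = 4.48.
- Effective n per arm: 6 × 175 / 4.48 = 234.4.
- Noncentrality: 0.375 × √(234.4 / 2) = 4.06.

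| Reference distribution | Power at two-sided 1% | Power at two-sided 5% |
|---|---|---|
| Normal | 93.1% | 98.2% |
| t, 10 df (unmatched) | 78.7% | 95.4% |
| t, 5 df (paired, no matching gain) | 56.6% | 89.6% |

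The t rows use the noncentral t distribution. Simulation of Trust means (400,000 replicates) gives 78.6% and 56.6% at the 1% level.

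**3. Unequal clusters.** With an assumed coefficient of variation of 0.4, the design effect is 1 + (1.16 × 175 − 1) × 0.02 = 5.04, effective n is 208.3 and noncentrality is 3.83. Power at 1% is 89.5% (normal), 72.8% (10 df) and 50.9% (5 df). The extra patients up to 3,000 therefore just about do their stated job under a normal approximation, but leave the degrees of freedom untouched.

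**4. Paired analysis with a matching gain.** Let matching remove a share r of between-Trust variance. The variance of a Trust mean, in SD² units, is 0.02 × (1 − r) + 0.98 / 175, and the noncentrality is 0.375 / √(2 × variance / 6). The values of r are assumptions, because the document gives none.

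| r | Noncentrality | Power at 1%, 5 df |
|---|---|---|
| 0 | 4.06 | 57% |
| 0.3 | 4.64 | 70% |
| 0.5 | 5.20 | 81% |
| 0.6 | 5.57 | 86% |
| 0.7 | 6.03 | 91% |

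Between 60% and 70% of the between-Trust variance must go before a paired analysis reaches 90%.

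**5. Can recruitment repair it?** With unlimited patients per Trust the variance of a Trust mean falls only to 0.02, so the noncentrality cannot exceed 0.375 × √(6 / (2 × 0.02)) = 4.59. Power at 1% on 10 df then stops at 89.0%.

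**The case against.** Several points can fairly be made for the plan.

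- **The 1% level is printed for Stage 2 only.** This is true, but 713 is exactly 211 × 3.38, the 3-point target is set for both comparisons, and the revision to 12 centres is said to keep the same power. The text gives Stage 1 no other level or power.
- **The shortfall is largely specific to 1%.** This stands. At two-sided 5%, which matches the planned 95% intervals, power is about 95% unmatched or 90% paired with no gain. At a coefficient of variation of 0.4 these become 93% and 86%. Also, at 1% on 10 df, power is 91% for 3.5 points and 97% for 4 points, both inside the range of 3 to 5 that the protocol calls important. This limits the consequence. It does not make the 90% at 1% for 3 points correct.
- **Matching may recover power.** It may. A reader might infer from the pairing that the design delivers only 57%. The document does not support that: it does not say that the pairs enter the analysis, and 57% also needs matching that achieves nothing. Nor does it support any particular gain.
- **Method details belong in the analysis plan.** Agreed. The protocol promises suitable cluster methods, and the choice of model or small-sample correction can be left to that plan. A reader might go further and argue that six pairs can never reach 1% in a randomisation test, or that a normal reference would inflate the type I error. The protocol plans neither, so neither is part of this point.
- **The data monitoring committee will review the assumptions.** That could revise the ICC or the loss rate. It adds no allowance for the number of Trusts. Power is sensitive to the ICC: on 10 df at 1% it is 96% at an ICC of 0.01 and 62% at 0.03.

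**Conclusion.** The point holds for the stated power basis. The implied 90% power at 1% for 3 points in Stage 1 rests on a normal critical value that 12 randomised Trusts do not justify. At the full 3,000 target, with the protocol's SD, ICC and loss, an unmatched analysis has about 79% with equal clusters and about 73% at an assumed coefficient of variation of 0.4. No recruitment within 12 Trusts brings the unmatched figure to 90%. For a paired analysis only a range can be given: about 57% with no matching gain to 91% if 70% of between-Trust variance is removed, with equal clusters.

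The document does not support the broader inference that Stage 1 is underpowered at any level. Judged at two-sided 5%, it has about 95% unmatched or 90% paired without gain. What is wrong is the combination of 90% and 1%, not the number of patients.

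**What to change.** In the Sample size section, do one of two things:

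1. Keep the 1% level for Stage 1 and restate its power with cluster-level t degrees of freedom: about 79% for an unmatched analysis at equal cluster sizes, with the value for the expected variation in cluster size beside it. Give a paired figure only as a range, with the assumed matching gain stated.
2. State that Stage 1 is powered at two-sided 5%, in line with the 95% intervals in the Statistical analysis section, and quote about 95% (10 df) or 90% (5 df, no matching gain), again with the allowance for unequal clusters.

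The cost is a few sentences. Under the first option the quoted power becomes less favourable; under the second the significance level does. Neither needs more patients or Trusts.
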